## Background

Dysphagia is as a common consequence of cerebral infarction, affecting at least 50% of stroke patients [1]. It often results in aspiration pneumonia, malnutrition and dehydration which are considered the most important secondary complication on the stroke unit [2]. Up to 50% of stroke patients suffer dysphagia 6 months from experiencing an ischaemic stroke [3]. Additionally, dysphagia causes numerous other secondary complications [4–6], contributing to substantial healthcare cost [7–9]. 

Dysphagia involves a complex pattern of swallowing dysfunction; the aetiology is heterogeneous [10]. The oropharynx is a highly sensitive structure transmitting information about the composition of the bolus to the cortex. Proper function of the tongue and muscles of the mouth floor is crucial for bolus formation and expulsion. In the hypopharynx, pressure dynamics and the contraction force of the pharyngeal muscles are essential for bolus expulsion into the oesophagus [11]. Damage to the muscles or nerves in this area can result in serious swallowing dysfunctions, increasing the risk of aspiration.

The complex protective mechanism of the upper airway during swallowing must operate precisely to protect the airway as the bolus is propelled into the oesophagus. Injuries or surgical interventions involving the hypopharynx and larynx are particularly critical. Dysphagia is commonly seen after prolonged intubation [12–14] and has been reported after the perioperative use of transoesophageal echocardiography (TEE) [15].

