## Outcomes

### Primary outcome

The primary outcome will assess the impact of the type and form of anaesthesia (intravenous vs. local) administered during TEE on swallowing in patients with ischaemic stroke and TIA, based on the aforementioned dysphagia scores [30–34].

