### Secondary outcomes

Comparison of TEE duration between patients with and without dysphagia and in cases of ischaemic stroke and TIA;Correlation between TEE duration and the degree of deterioration in FOIS-G and the experience of the TEE examiner in patients with ischaemic stroke and TIA;Correlation between TEE duration and TEE examiner’s experience in patients with ischaemic stroke and TIA;Interrater reliability in the evaluation of FEES.

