### Sample size estimation

Given the lack of existing data on the influence of anaesthesia type and form during TEE on swallowing in ischaemic stroke and TIA patients, this study is designed as a pilot trial. A total of 50 participants will be enrolled, with 25 patients in each group (stroke vs. TIA). The primary aim of this exploratory phase is to gather preliminary data to estimate effect sizes. These estimates will then serve as the basis for a formal power calculation and definitive sample size planning for a subsequent full-scale study.

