### Data collection and management

We will collect demographic information at baseline from the digital patient file. Symptom evaluation of stroke or TIA will be conducted by a neurological MD. Evaluation of cCT will be performed and documented by a neuroradiologist within the routine work-up of stroke. Within the routine stroke treatment stroke relevant scores National Institutes of Health Stroke Scale (NIHSS), Modified Rankin Scale (MRS) and Barthel Index (BI) will be documented. NIHSS is a 15-item assessment tool designed to evaluate stroke severity. According to the latest guidelines from the National Stroke Foundation, it is endorsed as a reliable instrument for assessing stroke severity in emergency department settings [35]. MRS is a clinician-reported tool that assesses global disability on a 7-point scale, ranging from no symptoms and perfect health to death. It is the most commonly used outcome measure in acute stroke trials [36]. BI is a ten-item scale used to assess the ability to perform activities of daily living (ADLs), including tasks like feeding, bathing, managing continence, mobility and dressing. It has been shown to have strong internal consistency and validity when evaluating functional status in elderly patients after cerebrovascular events [37]. Swallowing assessment within 24 h after admission to the stroke unit is conducted by an SLT. The 70-ml water swallow test is administred to define aspirations risk [38]. FEES is conducted prior to enrollment to the trial if the swallowing assessment confirms aspiration risk and is needed to provide adaqute dysphagia management and diet recommendations. Upon the enrollment in the trial following dysphagia relevant FEES scores are documented: SSRS, PAS, YS and FOIS-G [30–33].

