### Definition of dysphagia

Dysphagia is determined with the following cut-off values of the dysphagia scores:

Secretion Severity Rating Scale for Saliva Management (SSRS): SSRS ≥ 1; Penetration Aspiration Scale (PAS): PAS ≥ 3; Yale Pharyngeal Residue Severity Rating Scale: YS ≥ 3; Functional Oral Intake Scale (FOIS-G): FOIS-G < 7. Differences in patient-related data between the two groups: dysphagia/non-dysphagia group and intravenous vs. oral anaesthesia group are tested using Pearson’s chi-square test, Fischer’s exact test, *t*-test for independent samples or the Mann–Whitney *U*-test. For the purpose of logistic regression analyses, we intend to apply a median split to dichotomize the SSRS, PAS, YS and FOIS-G scores and create a binary outcome variable.

Assumptions for a *t*-test for independent samples are tested with the Levent test for variance homogeneity and the Shapiro–Wilk test including visual inspection of thedistribution plots for the assessment of normal distribution. If there is no homogeneity of variance or normal distribution, the Mann–Whitney *U* test for group differences is used. Correlations are calculated using the Pearson product-moment correlation or the Spearman rank correlation.

The inter-rater reliability between two raters is determined using a linearly weighted Cohen’s kappa, as this takes into account matches that could have arisen by chance on the one hand and places more weight on high non-matches on the other [39]. Furthermore, the percentage agreement and the Spearman rank correlation are specified for the agreement between two raters. In the case of a calculation of inter-rater reliability with more than two raters, a general agreement of all raters including subtraction of agreements by chance is calculated using Fleiss kappa [39].

Effect sizes are given according to Cohen’s d with a 95% confidence interval. *p*-values are given for all statistical results. The criterion for statistical significance is set at *p* < 0.05. Conclusions about clinically, practically and scientifically relevant correlations or differences are not made solely on the basis of the defined statistical significance [40].

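### Dysphagia is defined by absolute cut-offs and a median split with no stated use of the pre-TEE FEES 1 score, so dysphagia already present before TEE can be attributed to TEE duration or anaesthesia type

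*Protocol article*

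**What the plan says.** Table 1 of the protocol article places FEES 1 at T1 before TEE, and FEES 2 (T2) and FEES 3 (T3) after it. Data collection and management lists SSRS, PAS, YS and FOIS-G as the scores documented on enrolment.

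On outcomes, "The primary outcome will assess the impact of the type and form of anaesthesia (intravenous vs. local) administered during TEE on swallowing", judged by those scores. No examination is named. The first secondary outcome is "Comparison of TEE duration between patients with and without dysphagia". Another secondary outcome correlates TEE duration with the degree of deterioration in FOIS-G. That is the only place where a pre-TEE reference is implied.

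Definition of dysphagia sets the cut-offs SSRS ≥ 1, PAS ≥ 3, YS ≥ 3 and FOIS-G < 7. It continues: "Differences in patient-related data between the two groups: dysphagia/non-dysphagia group and intravenous vs. oral anaesthesia group are tested using" chi-square, Fisher, independent-samples t or Mann–Whitney tests. For logistic regression, the four scores are to be split at their median. Covariates are not listed.

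On who enters, the eligibility criteria exclude pre-existing neurogenic dysphagia without defining it. Data collection and management states that "FEES is conducted prior to enrollment to the trial if the swallowing assessment confirms aspiration risk" and is needed for management and diet. The Background describes dysphagia after cerebral infarction as "affecting at least 50% of stroke patients". The allocation section says the trial is not randomised and that groups follow diagnosis. The protocol does not assign anaesthesia.

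**The concern.** The Discussion says the trial aims to find which factors lead to dysphagic symptoms after TEE. That is a question about change across the procedure. An absolute cut-off or a median split applied to a post-TEE score answers a different question: who is dysphagic at that time, whatever the cause.

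A stroke patient who already had PAS ≥ 3 at FEES 1 and is unchanged at FEES 2 would join the dysphagia side of the TEE-duration comparison, and would count as a poor outcome for whichever anaesthesia was given. Because anaesthesia is not randomised, nothing balances pre-TEE dysphagia between the anaesthesia groups.

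The stake is the pilot's declared product: "The primary aim of this exploratory phase is to gather preliminary data to estimate effect sizes", as the basis for sizing the full study. A biased effect size carries forward into that calculation.

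**Working it through.** The article gives no power, effect size or standard deviation, so there is no figure of its own to reproduce. The steps below show possible size only.

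**1. Use of FEES 1, place by place**
- Dysphagia definition: absolute cut-offs, no FEES 1 reference.
- Group tests: independent samples, no time point.
- Logistic outcome: median split, no time point, covariates unlisted.
- Primary outcome: refers to the scores only.
- FOIS-G deterioration: implies a pre-TEE value, but covers one of four scales and is a correlation, not a group comparison.

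**2. Patients dysphagic before TEE**

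Inputs: 25 stroke patients (Sample size estimation); 50% from the Background as a general stroke figure; 25% as an assumed lower value, because the exclusions (aphasia, delirium, lack of alertness and others) may remove severe strokes.
- 25 × 0.25 = 6.25
- 25 × 0.50 = 12.5

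So about 6–12 of 25 would be classed as dysphagic with no TEE effect.

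**3. Share of post-TEE dysphagia that was there before**

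Assume that none resolves, that TIA prevalence before TEE is p, and that a fraction q of the remaining patients is newly dysphagic. With pre = 25 × (stroke prevalence) + 25p, the share is pre / [pre + (50 − pre) × q].
- Stroke 50%, p = 0, q = 0.2: 12.5 / (12.5 + 7.5) = 62.5%
- Stroke 50%, p = 0 to 0.2, q = 0.1 to 0.3: 53% to 84%
- Stroke 25%, p = 0, q = 0.2: 6.25 / (6.25 + 8.75) = 42%

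**4. Effect on the TEE-duration comparison**

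Suppose newly dysphagic patients differ in mean TEE duration by Δ from everyone else, and pre-TEE dysphagia is unrelated to duration. The observed difference is then (1 − share) × Δ. That is 0.375Δ at a share of 62.5% and 0.58Δ at 42%. If pre-TEE dysphagia is related to duration, the bias can go either way.

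**5. Effect on the anaesthesia comparison**

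Assume no anaesthesia effect and 20% new dysphagia in both groups. The post-TEE proportion is a + (1 − a) × 0.2, where a is the pre-TEE proportion.
- 20% vs 30% before: 0.36 vs 0.44; OR = (0.44/0.56)/(0.36/0.64) = 1.4
- 15% vs 35% before: 0.32 vs 0.48; OR = (0.48/0.52)/(0.32/0.68) = 2.0

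**6. Precision, linear model only**

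Adjusting for FEES 1 removes r² of the residual variance, where r is the assumed FEES 1–FEES 2 correlation: 9% at 0.3, 25% at 0.5, 49% at 0.7. The detectable difference at 25:25 (assumed split), two-sided 5% (sidedness assumed) and 80% power is (1.96 + 0.84) × √[(1 − r²) × 2/25]. This gives 0.79 SD unadjusted, and 0.76, 0.69 and 0.57 SD at r = 0.3, 0.5 and 0.7.

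**The case against.** The strongest reply is that this is a condensed article and much of the concern rests on silence. It names no FEES time point, an independent-samples test can be run on change scores, and the logistic regression could include FEES 1 among its unlisted covariates. A full protocol or analysis plan may say so. The sentence on group differences also literally concerns patient-related data, which Statistical methods lists as age, gender, diagnosis, medication, TEE duration and anaesthesia form. Swallowing scores are not in that list.

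This stands in part. A reader might infer that the plan commits to a cross-sectional comparison at one examination. The text does not say that, and it neither includes nor rules out FEES 1 in the regression. But the absolute cut-offs and the median split are stated choices, and neither refers to the pre-TEE state. The same sentence uses the cut-off-defined dysphagia grouping, and it is the only group-comparison plan given.

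A second reply is that pre-existing neurogenic dysphagia is excluded. If that covered index-stroke dysphagia, most of the problem would go. The term is undefined, however, and the provision for FEES and diet management before enrolment, without making the result an exclusion, makes the other reading likelier. It does not settle the matter.

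Third, the Background's 50% describes stroke patients in general. It is not tied to these cut-offs or to a sample narrowed by the exclusions and a TEE indication. This is correct, and is why a range is shown.

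Finally, this is a pilot that says it will not judge relevance on significance alone. That lowers the severity. It does not protect the effect sizes.

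**Conclusion.** The point holds as a should-fix. As written, the dysphagia definition, the group tests and the logistic outcome make no stated use of FEES 1. With non-randomised anaesthesia and probable entry of patients with index-stroke dysphagia, pre-TEE dysphagia can be read as an effect of TEE duration or anaesthesia type.

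The size depends on assumptions. At 25–50% pre-TEE prevalence in stroke, about 6–12 of 25 stroke patients are misattributed, and moderate imbalance between anaesthesia groups yields a spurious odds ratio of 1.4 to 2.0. The documents do not establish these rates.

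Two stronger readings are not supported. A reader might infer that every interval in the trial is wider than it need be. Inter-rater kappa and the correlation of TEE duration with examiner experience have no FEES 1 value to adjust for. A reader might also carry the r² gain over to the whole analysis. It applies to a linear baseline-adjusted model with an assumed r, is small at r = 0.3, and does not transfer directly to an ordinal or logistic model. The main gain is less confounding, not precision, and adjustment for FEES 1 will not remove all confounding. The data are recoverable, because FEES 1 is on the schedule.

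**What to change.** - Name the post-TEE FEES used for the primary comparison.
- In the anaesthesia comparison, including the planned logistic regression, enter the FEES 1 score of the same scale as a covariate.
- In the TEE-duration comparison, replace the split into patients with and without dysphagia by new or worsened dysphagia relative to FEES 1.
- State whether dysphagia from the index stroke falls under the exclusion of pre-existing neurogenic dysphagia.

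An ordinal repeated-measures model that adds FEES 3 is optional and may be unstable with 50 patients and an unknown anaesthesia split. A plain change score is a weaker substitute for precision: its variance factor is 2(1 − r), which is 1.4 at r = 0.3, worse than using the post-TEE score alone.

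The cost is a change of wording and one extra model term in a 50-patient sample. No new data are needed.

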### Eligibility criteria

A total of 50 patients will be recruited from the UKGM stroke unit, comprising 25 with ischaemic stroke and 25 with TIA.

The inclusion criteria are (1) ischaemic stroke occurring no more than 7 days prior, confirmed by cranial computed tomography (cCT) or magnetic resonance imaging (MRI); (2) for TIA: presence of a perfusion deficit in cCT or clinical diagnosis of TIA by a physician with focal neurological deficits still persisting at the time of presentation; (3) indication for TEE in both groups; (4) written informed consent to participate.

Exclusion criteria include (1) pre-existing neurogenic dysphagia; (2) prior surgery or chemoradiotherapy for head and neck tumours; (3) cervical spine surgery; (4) thyroid gland surgery; (5) aphasia; (6) acute delirium; (7) lack of compliance; (8) lack of alertness; (9) dementia; (10) existing legal guardianship.

TEE will be performed by cardiologists from the Department of Cardiology at UKGM. FEES will be conducted by neurologists and/or speech and language therapists (SLT) from the Department of Neurology at UKGM.

Trial participants or authorized surrogates will be informed in detail and comprehensibly both in a written consent form as well as in a personal interview by the medical investigator from the Department of Neurology about the treatment method to be tested and the comparative method as well as about the nature, significance, risks and scope of the clinical trial.

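### The logistic-regression outcome is cut at the sample median although the same section fixes clinical cut-offs for the same scores, so the modelled event depends on the sample and can contradict the plan's own definition of dysphagia

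*Protocol article*

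**What the plan says.** All the relevant text is in the Protocol article. Under Definition of dysphagia, the plan states "Dysphagia is determined with the following cut-off values of the dysphagia scores" and lists "Secretion Severity Rating Scale for Saliva Management (SSRS): SSRS ≥ 1", then "PAS ≥ 3; Yale Pharyngeal Residue Severity Rating Scale: YS ≥ 3", then "Functional Oral Intake Scale (FOIS-G): FOIS-G < 7". The resulting groups are used for the univariate comparisons of patient-related data: "dysphagia/non-dysphagia group and intravenous vs. oral anaesthesia group are tested using" chi-square, Fisher, t or Mann–Whitney tests.

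The next sentence turns to logistic regression and sets a different rule for the same four scores: "we intend to apply a median split to dichotomize the SSRS, PAS, YS and FOIS-G scores and create a binary outcome variable". It gives no reason for a second threshold and does not say on which side of the split a score equal to the median falls.

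The section on dysphagia severity assessment describes SSRS, PAS, YS and FOIS-G as scales of 4, 8, 5 and 7 points. Eligibility criteria sets the sample: "A total of 50 patients will be recruited from the UKGM stroke unit, comprising 25 with ischaemic stroke and 25 with TIA". Sample size estimation gives the pilot's purpose, which is to estimate effect sizes: "These estimates will then serve as the basis for a formal power calculation" of a later full-scale study.

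**The concern.** One section holds two binary definitions of the same scores. The first is clinical and fixed. The second is relative: a patient is an event if worse than this sample's middle patient. Logistic regression is the only regression model the plan names for these scores, so the definition used for modelling is the one that moves with the sample.

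Two things are at stake. The first is consistency within the report. A patient with PAS 2 could be non-dysphagic in the group comparisons and an event in the regression. The second is transfer to the next study. An odds ratio for being worse than the pilot's median has no fixed event, and the full-scale study will have its own median.

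Short ordinal scales aggravate this. Many patients share the same value, so the unstated handling of ties can decide the outcome for a large part of the sample.

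**Working it through.** **What the text alone shows.** Four fixed cut-offs and one median rule apply to the same four scores, with no reason given for the difference. This part needs no assumption.

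**Inputs for the size of the problem.** From the documents: n = 50 (25 stroke, 25 TIA), the scale lengths and the fixed cut-offs. SSRS is taken as 0 to 3, because its cut-off is ≥ 1. The documents give no score distribution, so every distribution below is an assumption. The plan states no figure on this point that could be reproduced.

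**Step 1: when does the median fall in the best category?** With n = 50 this needs at least 26 patients there. If a share p scores in the best category, the probability is P(Bin(50, p) ≥ 26). For a median taken within one cohort of 25 it is P(Bin(25, p) ≥ 13).

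| Assumed p | n = 50 | n = 25 |
|---|---|---|
| 40% | 0.06 | 0.15 |
| 50% | 0.44 | 0.50 |
| 60% | 0.90 | 0.85 |
| 70% | 0.998 | 0.98 |

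As a guide to plausible p, the Background puts dysphagia at about half of stroke patients or more. Take 50% of the stroke patients as outside the best category, and assume 0, 10, 20, 30 or 50% of the TIA patients. The overall share in the best category is then 75, 70, 65, 60 or 50%, and the probability is 1.00, 0.999, 0.98, 0.91 or 0.44. This equates dysphagia with any score outside the best category. By the plan's cut-offs that is exact only for SSRS and FOIS-G.

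**Step 2: what the split does in that case.**

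| Score | Plan's cut-off | Worse than median | Median or worse |
|---|---|---|---|
| SSRS | ≥ 1 | ≥ 1 (same) | all patients |
| PAS | ≥ 3 | ≥ 2 (differs) | all patients |
| YS | ≥ 3 | ≥ 2 (differs) | all patients |
| FOIS-G | < 7 | < 7 (same) | all patients |

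In the last column one class is empty and no logistic model can be fitted.

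**Step 3: when the best category holds less than half.** Simulation with n = 50 and an assumed 45% at PAS 1 (the rest .15/.12/.08/.07/.05/.04/.04) gave a sample median of 1, 1.5, 2, 2.5 or 3 in 19.7, 8.7, 61.7, 4.3 and 5.6% of samples. With the event defined as worse than the median, the threshold is:

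- PAS ≥ 2 in 19.7 + 8.7 = 28.4% of samples
- PAS ≥ 3 in 61.7 + 4.3 = 66.0%
- PAS ≥ 4 in 5.6%

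The event thus changes between samples from one population.

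**Step 4: disagreement with the fixed cut-offs.** Over 11 assumed distributions for the four scores, the worse-than-median split classed 0 to 35% of patients differently from the plan's cut-off. The median-or-worse split did so for 1 to 70%. An empty class never arose with the first split. With the second its probability ran from 0 to 0.998.

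**Step 5: information lost by dichotomising.** Under proportional odds, the information in a binary split relative to the full score is (1 − Σ cubed split shares) / (1 − Σ cubed category shares).

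- Assumed PAS shares .35/.20/.12/.10/.08/.06/.05/.04: the population median is 2, so worse than median is PAS ≥ 3, the plan's own cut-off. Both give (1 − .55³ − .45³) / .9455 = 0.785.
- Assumed PAS shares .60/.15/.08/.05/.04/.03/.03/.02: the denominator is 1 − .2201 = .7799. PAS ≥ 2 gives (1 − .60³ − .40³) / .7799 = 0.92. PAS ≥ 3 gives (1 − .75³ − .25³) / .7799 = 0.72.

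Information loss is therefore no argument for the fixed cut-offs over the median split. It is an argument for an ordinal model.

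**The case against.** A fair defence runs as follows. The split is confined to the logistic regressions, and the fixed cut-offs still define the groups for the univariate tests. No primary or secondary outcome is tied to logistic regression. The plan reports effect sizes as Cohen's d and nowhere says that odds ratios will feed the power calculation. This is an exploratory pilot without a power claim. A median split also guards against very few events and, as Step 5 shows, can retain more information than the clinical cut-off. All of this stands, and it limits the point to one modelling step.

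Three stronger readings are tempting, and the documents do not support them.

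- A reader might infer that the scores will pile up at the best category. No distribution is given. The TIA half and the exclusion of pre-existing neurogenic dysphagia point that way. The stated dysphagia rate in stroke and the rise in scores after TEE reported for the first trial point the other way.
- A reader might infer that the regression will have an empty class. That needs both a majority in the best category and ties assigned to the worse class. The plan states neither.
- A reader might infer that the cut point will change between visits, cohorts and bolus consistencies. The text does not say that the median is recomputed for each, and a single pooled median fits it equally well.

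The defence does not supply a reason for two definitions or a rule for ties, and it does not make the event reproducible in another sample.

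**Conclusion.** The point holds in a limited form. It is certain from the text that the logistic-regression outcome follows a sample-dependent rule that can differ from the dysphagia definition in the same section, and that neither a reason nor a tie rule is given. How far it would differ rests on assumed distributions. The probability that the median of 50 patients lies in the best category runs from 0.06 (40% there) to 0.998 (70% there). In that case PAS 2 and YS 2 become events against the plan's definition, or one class is empty, depending on how ties are handled. At best the split reproduces the stated cut-offs. At worst it contradicts them or cannot be fitted.

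This should be fixed, but it does not invalidate the study. It affects one analysis step in a pilot. It matters mainly because estimates that carry over to the full-scale study are what the pilot is meant to deliver.

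**What to change.** Delete the median-split sentence. State that wherever a logistic regression is fitted, the binary outcome for each score is the cut-off already listed in that section, the same at every visit and in both cohorts.

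Optionally, add a proportional-odds model on the full SSRS, PAS, YS and FOIS-G scores, with sparse categories merged. This recovers the information that any dichotomy loses, including the fixed cut-offs. It brings its own assumption and needs care with up to 8 levels in 50 patients.

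The cost is about one sentence, submitted under the protocol's own amendment rules and settled before scores are analysed. The downside is that if few patients pass a fixed cut-off, that model has few events. In the assumed scenarios the cut-offs classed 25 to 65% of patients as dysphagic, about 13 to 33 of 50, so at the lower end a model could carry very few covariates.

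### TEE duration is correlated with examiner experience patient by patient, although experience belongs to the examiner; if durations cluster by examiner, the nominal 5% test rejects too often

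*Protocol article*

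**What the plan says.** All references are to the protocol article.

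- **Secondary outcomes** lists "Correlation between TEE duration and TEE examiner’s experience in patients with ischaemic stroke and TIA". Another item in the same list reads "Correlation between TEE duration and the degree of deterioration in FOIS-G and the experience of the TEE examiner". That second item does not make clear which pairs of variables are to be correlated.
- **Eligibility criteria** states who does the procedure: "TEE will be performed by cardiologists from the Department of Cardiology at UKGM". The number of cardiologists, their caseloads and the measure of experience are not given.
- **Definition of dysphagia** (under Statistical methods) names the method: "Correlations are calculated using the Pearson product-moment correlation or the Spearman rank correlation". P-values accompany all results, and "The criterion for statistical significance is set at *p* < 0.05". No examiner-level analysis, random effect or cluster adjustment is named. A 95% confidence interval is mentioned only for Cohen's d. The section adds that conclusions about relevance will not rest on significance alone.
- **Sample size estimation** sets 50 patients, 25 with stroke and 25 with TIA, and describes a pilot: "The primary aim of this exploratory phase is to gather preliminary data to estimate effect sizes".

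**The concern.** The Pearson and Spearman tests take their reference distribution from the number of independent pairs. Experience does not vary freely from patient to patient. Every patient of one cardiologist carries that cardiologist's value, or nearly so over the roughly 13 months between the start of recruitment and planned completion given under Trial status. TEE duration plausibly also depends on who holds the probe. When both variables share the examiner as a source of variation, 50 patients carry less information about experience than 50 independent pairs would, and the test does not know this.

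The working habits of one or two cardiologists could then appear as a significant effect of experience. Examiner experience is one of the four parameters listed under Objectives, and the pilot's estimates are meant to feed the planning of a full-scale study. Overstated evidence here could carry forward.

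**Working it through.** **Plan's own figure.** There is none to reproduce. The sample size is a pilot number without a power calculation.

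**Inputs from the article.** N = 50 (25 per diagnosis); significance level 0.05, taken as two-sided because sidedness is not stated; plain Pearson or Spearman correlation; one cardiology department.

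**Assumptions not in the article.** k = 5 or 12 examiners with equal caseloads m = N/k; experience constant within examiner; ICC of the outcome within examiner from 0 to 0.20; no true association.

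**Formulas.** Design effect DE = 1 + (m − 1) × ICC. Effective sample = N/DE. Approximate true error = 2 × [1 − Φ(1.96/√DE)].

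**Worked example, 5 examiners, ICC 0.10.** m = 50/5 = 10. DE = 1 + 9 × 0.10 = 1.90. Effective sample = 50/1.90 = 26.3. 1.96/√1.90 = 1.42, so the approximate error is 0.155. Simulation with 4,000 null data sets gave 0.165 for Pearson and 0.158 for Spearman.

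| Examiners (patients each) | ICC | DE | Effective n | Error, formula | Error, simulated (Pearson) |
|---|---|---|---|---|---|
| 5 (10) | 0.02 | 1.18 | 42.4 | 0.071 | 0.074 |
| 5 (10) | 0.05 | 1.45 | 34.5 | 0.104 | 0.102 |
| 5 (10) | 0.10 | 1.90 | 26.3 | 0.155 | 0.165 |
| 5 (10) | 0.20 | 2.80 | 17.9 | 0.241 | 0.242 |
| 12 (about 4.2) | 0.02 | 1.06 | 47.0 | 0.057 | 0.064 |
| 12 (about 4.2) | 0.05 | 1.16 | 43.2 | 0.069 | 0.063 |
| 12 (about 4.2) | 0.10 | 1.32 | 38.0 | 0.088 | 0.098 |
| 12 (about 4.2) | 0.20 | 1.63 | 30.6 | 0.125 | 0.131 |

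The Monte Carlo standard error near 0.05 is √(0.05 × 0.95/4000) = 0.003.

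**Checks.**

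- *No clustering (ICC 0):* the simulated error is 0.052 for 5 examiners and 0.048 for 12, so the test is sound in that case.
- *Run within one diagnosis group (N = 25), 5 examiners, ICC 0.10:* m = 5, DE = 1 + 4 × 0.10 = 1.40, simulated error 0.102.
- *Unequal caseloads, 5 examiners, ICC 0.10:* 0.169, close to the equal-caseload result.
- *TEE duration against FOIS-G change, both measured per patient:* simulated error 0.05 to 0.08, so this pair is little affected.
- *Correlation of examiner means with k − 2 degrees of freedom:* simulated error 0.04 to 0.06 in every scenario.

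**What the examiner-level test can detect.** The critical correlation is t/√(t² + df). For 5 examiners (df 3, t = 3.182) it is 3.182/√(10.125 + 3) = 0.88. For 12 examiners (df 10, t = 2.228) it is 2.228/√(4.964 + 10) = 0.58. For 3 examiners (df 1, t = 12.706) it is 0.997, so a p-value is of no practical use there. These are correlations of means and are not on the same scale as a patient-level correlation.

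**The case against.** The size of the inflation rests entirely on inputs the article does not give. At a low ICC or with many examiners the test is near its nominal level: 12 examiners at ICC 0.05 give about 0.06. These are secondary outcomes of an exploratory pilot, and the article itself limits the weight put on significance. The article is condensed, and an analysis plan that is not shown might handle clustering. All of this stands and limits the importance of the point. It does not remove it: the article names a method for this item, the method does not fit an examiner-level variable, and p-values will be reported from it.

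Several stronger readings are tempting but not supported:

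- *Only a few cardiologists do the TEEs.* The article says one department, not how many examiners. The direction of the error does not depend on few examiners, but its size does.
- *Confidence intervals will be too narrow.* The only interval named is for Cohen's d; none is named for correlations.
- *The effective sample is close to the number of examiners.* For 5 examiners it is about 18 to 42 over the ICC range shown. It would approach 5 only as the ICC approached 1.
- *FOIS-G deterioration is certainly tested against experience.* The wording is ambiguous, and examiner clustering is less certain for an oral-intake score than for procedure time.
- *The test always uses all 50 patients.* The item may equally mean a separate correlation in each diagnosis group, where the inflation is smaller.

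**Conclusion.** The point holds conditionally. For TEE duration against examiner experience, the stated patient-level test rejects too often whenever examiners do several TEEs each and durations cluster by examiner. With 5 assumed examiners, a modest ICC of 0.05 doubles the error to about 0.10; with 12, it takes an ICC of about 0.10 to do so. The duration and experience item is explicit in the article. The link between experience and FOIS-G depends on how an unclear sentence is read. Nothing in the article shows that the inflation will in fact occur, since an ICC of zero would remove it. The matter deserves correction because experience is a declared objective and the change is small, but no primary conclusion depends on it.

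**What to change.** For the items that involve experience, replace the patient-level Pearson or Spearman test by an examiner-level analysis:

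1. Correlate examiner means with experience, using k − 2 degrees of freedom for k examiners. If there are enough examiners, a mixed model for log TEE duration with a random examiner intercept and small-sample degrees of freedom is an alternative. With about 5 examiners the random-effect variance would be poorly estimated.
2. Report the number of examiners and the number of patients per examiner beside the result, and state how experience is measured.
3. If there are very few examiners, describe experience without a p-value. A permutation test does not rescue this case: 3 examiners allow only 3 × 2 × 1 = 6 arrangements, so the smallest attainable p-value is 1/6 = 0.17.
4. State whether FOIS-G deterioration is to be related to experience. If so, treat it at examiner level too, with a method suited to a 7-level ordinal score.
5. State whether the correlations are pooled or run within each diagnosis group.

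The cost is a change of analysis wording and an examiner code in the data set, which should be easy to add because assigning experience already requires knowing who performed each TEE. The downside is less precision for an exploratory secondary outcome, and possibly no usable test at all if the department relies on very few examiners.
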